### Outcome assessment

Outcome measures will be assessed at five time points through an online link powered by Wenjuanxing (www.wjx.cn, a website like Surveymonkey), namely at baseline (T0), post-intervention/consultation (T1), 1 month (T2), 3- and 6-months (T3 and T4) follow-up after the randomization.

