### eHealth intervention group

Participants assigned to the intervention group will, in addition to usual care, receive an invitation QR code via WeChat messenger to access the eHealth patient education tool built within the WeChat mini programs platform. Participants register themselves using a username and password. The intervention includes instructions on how to efficiently use the tool, information detailing the knowledge of knee osteoarthritis and the recommendations of clinical guidelines including level of evidence supporting each recommendation [24], and advice on healthy lifestyle, in a scheduled video conference with a physiotherapist using Tencent Meeting app (Tencent Holdings Ltd., Shenzhen, China) on a smartphone, a tablet or computer. Participants will be provided with a welcome brochure with an overview of the intervention components, and instructions on how to register and use the eHealth patient education tool and Tencent Meeting app (Web browser, Android or iOS app) at home. The intervention will be delivered within 7 days after the randomization, during which the video consultation with a physiotherapist will last up to 90 min according to the patient’s preference. Automatically generated push notifications within WeChat messenger will be sent to motivate participants to review the information and use the tool twice a week after the consultation for at least 6 months. Additionally, participants have the possibility to get help from the coordinators or via the study hotline regarding any technical problems when using the tool.

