An iterative method of collaboration-based persuasive design between healthcare providers and patients is employed to the development of the eHealth patient education tool [18]. In brief, a focus group (*n* = 6, involved 3 patients with knee osteoarthritis, 2 physiotherapists and 1 physiatrist) was initially conducted in two phases during the development process, in which healthcare providers met at Phase I to provide input on the eHealth prototype regarding design and content and patients were invited to Phase II to discuss with healthcare providers regarding literacy demands and usability. Then a pilot-testing of the developed tool will be done among healthcare providers and patients (with a total of 20 participants) in a similar way to the focus group, and the testing version could be found in Additional file 2. The tool includes the following features:**Education Center:** information on knee osteoarthritis and treatment options (details could be found in Additional file 2), based on the recommendations of clinical guidelines; exercise advice and videos; physical activity and well-being advice.**Personal Information:** the option to record demographic data and history of knee osteoarthritis.**Self-Management:** self-monitor symptoms during the study; log the planned care received for knee osteoarthritis and other comorbidities.**Schedule and Plan:** set reminders and develop a calendar for the scheduled consultation, and assessments.**Communication and Help Center:** contact with an assigned physiotherapist or healthcare professional; an overview of the educational tool.

Participants who cannot attend the consultation will be excluded after contact has been attempted three times. One day after the consultation with the physiotherapist, all participants will receive the follow-up questionnaires on their WeChat. A reminder will be sent if participants are found non-responding after 1 week. Intervention fidelity will be assessed to rate the degree of involvement of a patient within 24 h after the physiotherapist-delivered consultation. As a participant reads information or watches a video, analytics built into the server website will collect data on what type of information and how long the participant spent on that. The chief research coordinator, program developer, and research assistance conducting data collection have access to the website and are able to view the analytics for each participant.

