#### Primary outcome

Primary outcomes included knowledge about disease and treatment options. The validated osteoarthritis (OA) patient knowledge questionnaire (PKQ-OA) [25] will be used, modified, and adapted to reflect the key learner content covered in the eHealth patient education tool. The questionnaire comprises 7 single choice and 14 multiple choice questions with 31 correct answers and details of the questionnaire could be found in Additional file 4. We modified the PKQ-OA closely according to the patient education information provided in the education center and the questions are relevant with the evidence-based information. Total knowledge scores will be obtained by summing the scores, range from 0 to 21. Five patients with knee osteoarthritis and three healthcare professionals will provide input on the prototype of eHealth tool regarding design, content and usability, from which data collected will be used to finalize the tool for the trial. Higher scores indicate greater disease knowledge, and scoring above 50% on the knowledge portion of the questionnaire will be classified as adequately informed [26].

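### The knowledge test at T1 to T4 is taken remotely while only the intervention arm has the matching content to hand, so look-up may inflate the primary difference

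*Protocol article*

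**What the plan says.** **How the outcome is collected.** Under Outcome assessment: "Outcome measures will be assessed at five time points through an online link powered by Wenjuanxing". These are baseline (T0), post-consultation (T1), and 1, 3 and 6 months after randomization (T2 to T4). For the questionnaire sent one day after the consultation, the eHealth intervention group section says that "all participants will receive the follow-up questionnaires on their WeChat", and then: "A reminder will be sent if participants are found non-responding after 1 week". No supervised sitting or time limit is described.

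**Where the content sits.** Intervention participants receive a QR code "to access the eHealth patient education tool built within the WeChat mini programs platform". Push notifications are "sent to motivate participants to review the information and use the tool twice a week after the consultation for at least 6 months". The control arm receives usual care, including verbal information, without the tool.

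**How the test relates to the tool.** Under Primary outcome: "We modified the PKQ-OA closely according to the patient education information provided in the education center". The score runs from 0 to 21.

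**What it is meant to measure.** The Aim section sets the primary objective as patient knowledge: how far patients understand the condition and the efficacy of non-drug treatment options.

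**What is logged.** In the tool, "analytics built into the server website will collect data on what type of information and how long the participant spent on that". The Other measures section uses these data to describe utilization.

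**The concern.** At each follow-up an intervention participant can have the test and its source material within reach at the same time, and the source belongs to one arm only. The consultation falls within 7 days after randomization and the prompts continue for at least 6 months after it. The prompted period therefore reaches T4 and covers all four follow-ups. T0 precedes tool access and should be unaffected.

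A correct answer copied from the Education Center scores the same as one that was understood. The difference between arms would then mix learning with access to the answers, and the error would favour the tool on the primary outcome. Randomization, intention-to-treat analysis and the covariates listed under Statistical analysis do not remove this, because it arises after allocation and from the way the outcome is measured. It is also hard to undo once the scores are in.

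**Working it through.** **Inputs from the documents.** Correct response rates of 55.3% and 39.5%, 108 per group and 20% dropout (Sample size); score range 0 to 21 (Primary outcome).

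**Assumptions, because the documents give no figure.** The share f of the intervention arm that looks answers up; the score c such a participant reaches (80% to 100%); no look-up among controls unless stated.

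**1. Planned effect.** 55.3 − 39.5 = 15.8 percentage points. Read as a share of the 21-point scale, 0.158 × 21 = 3.3 points.

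**2. Look-up share that reproduces it with no learning.** With base score b = 39.5% in both arms, the spurious difference is f × (c − b). Setting it to 15.8 gives f = 15.8 / (c − 39.5):

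- c = 80%: 15.8 / 40.5 = 39%
- c = 90%: 15.8 / 50.5 = 31%
- c = 100%: 15.8 / 60.5 = 26%

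**3. Smaller shares, same base, c from 80% to 100%.**

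- f = 5%: 2.0 to 3.0 percentage points
- f = 10%: 4.05 to 6.05 percentage points
- f = 20%: 8.1 to 12.1 percentage points

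**4. If those who look up have also learned.** With b = 55.3% and f = 10%:

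- c = 90%: 0.10 × (90 − 55.3) = 3.5 points
- c = 80%: 0.10 × (80 − 55.3) = 2.5 points
- c = 100%: 0.10 × (100 − 55.3) = 4.5 points

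**5. If controls search the web.** The net bias is f_I(c_I − b) − f_C(c_C − b), where I and C denote the arms. It vanishes if both arms look up equally often and equally well. It stays positive if the intervention arm looks up more often or finds better answers.

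**6. What a small share could do to the test.** Completers per arm: 108 × 0.8 ≈ 86. With no true effect, the chance of a significant result in favour of the tool is Φ(δ / (v√(2/86)) − 1.96). Here δ = f(c − b) and v² = s² + f(1 − f)(c − b)²/2, which averages the variances of the two arms. Take f = 10%, c = 90%, b = 39.5%, so δ = 5.05 points. The score SD s is assumed. The largest value below, 31.6 points, is the SD implied if 15.8 points is the plan's 0.5 SD.

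- s = 15: v = 18.4, chance 44%
- s = 25: v = 27.2, chance 23%
- s = 31.6: v = 33.4, chance 17%

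The nominal figure in that direction is 2.5%.

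**The case against.** **The article is condensed.** The questionnaire is in Additional file 4, which is not shown, and a closed-book line could stand there. The content of the instructions that an assistant gives controls on completing the questionnaires is not shown either. This stands as a caution: if such an instruction exists, that part of the fix is already met. The point itself rests on what the article does fix: remote collection, items adapted to the tool, and concurrent access in one arm. An instruction would reduce that asymmetry but not remove it.

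**Look-up is not shown to happen.** Correct. A reader might infer that the effect will be inflated, or that a positive result would be an artefact. The documents support neither: they give no look-up rate, describe no reward for a high score, and keep the study hypotheses from participants. That the test is unsupervised is itself inferred from remote delivery.

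**Controls can look things up too.** Also correct. Owning an internet-capable device with access is an inclusion criterion, and the tool's content draws on clinical guidelines. It would be wrong to say that controls have no source. The offset is likely to be partial, because the items follow the tool's own content.

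**WeChat delivery is stated only for the post-consultation questionnaire.** For T2 to T4 the text says only that an online link is used. Delivery in the same app is a reasonable reading there, and the mechanism does not need it.

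**Consulting the tool is part of its benefit.** That is a defensible aim, but it is access to information, whereas the Aim section names understanding.

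**Conclusion.** The concern holds as a risk of bias of unknown size, in favour of the tool, on the knowledge score at T1 to T4. A reader might extend it to every post-baseline comparison; that goes too far, because satisfaction and trust cannot be looked up in the Education Center.

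The 26% to 39% range rests on no learning, no control look-up, a base of 39.5% and look-up scores of 100% to 80%. It shows what the mechanism could do, not how likely it is. Starting from the planned 55.3%, the addition is smaller, at about 3.5 points per 10% looking up at a 90% score. Control look-up would reduce either figure. The significance calculation further assumes the score SD. Since modest shares could matter and prevention at collection is easier than later correction, the measurement procedure should be changed before follow-up scores are collected.

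**What to change.** 1. Give both arms the same instruction to answer the PKQ-OA without consulting any material, and require completion in a single session, at every time point including baseline.
2. Where technically feasible, make the Education Center unavailable to a participant while the test is being completed. The questionnaire runs on Wenjuanxing and the tool is a WeChat mini program. The documents show no link between the two, so the sponsor should establish whether a lock can be triggered. A lock reduces look-up but does not stop use of screenshots or a second device.
3. If the Education Center is not locked, confirm whether the analytics keep clock times of access; the article mentions only content type and time spent. If they do, pre-specify a sensitivity analysis that keeps all randomised participants and treats knowledge scores with Education Center access during the test conservatively, for example by substituting the baseline score. Report it as a bound and not as the primary estimate, because it can penalise only the intervention arm.

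The cost is one instruction line and a single-session requirement on the questionnaire, some programming work if the lock is used, a brief loss of access to content during each test, and possibly a smaller observed effect.

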#### Primary outcome

Primary outcomes included knowledge about disease and treatment options. The validated osteoarthritis (OA) patient knowledge questionnaire (PKQ-OA) [25] will be used, modified, and adapted to reflect the key learner content covered in the eHealth patient education tool. The questionnaire comprises 7 single choice and 14 multiple choice questions with 31 correct answers and details of the questionnaire could be found in Additional file 4. We modified the PKQ-OA closely according to the patient education information provided in the education center and the questions are relevant with the evidence-based information. Total knowledge scores will be obtained by summing the scores, range from 0 to 21. Five patients with knee osteoarthritis and three healthcare professionals will provide input on the prototype of eHealth tool regarding design, content and usability, from which data collected will be used to finalize the tool for the trial. Higher scores indicate greater disease knowledge, and scoring above 50% on the knowledge portion of the questionnaire will be classified as adequately informed [26].

#### Secondary outcome

The secondary outcome measures will track patient satisfaction with the consultation, the eHealth patient education tool, and their trust of the physiotherapist. Maintaining a similar format as the adopted survey [27], the questionnaire comprises 6 closed questions and 2 open questions for participants in both groups and details of the questionnaire could be found in Additional file 4.

#### Other measures

Participants’ demographic data, history of diseases and health behavior information will also be collected. Potential “inadequate health literacy level” in participants will be screened using 3 questions: “how confident are you filling out questionnaires by yourself?” (“Confident with Questionnaires”), “Do you need someone to help you read? If yes, how often?” (“Read Assistance”) and “Do you have obstacles learning about your medical condition due to your inability to read? If yes, how often?” (“Problem Reading”) [28, 29]. In the process evaluation, measures of recruitment rate, attendance and follow-up rate will be monitored and recorded. Reasons for exclusions, declining participation and the drop-out of participants will be noted through the trial.

Participants in the eHealth intervention group will receive additional questions on the usability of the tool, including 13 closed questions and 3 opened-ended questions [30] and details of the questionnaire could be found in Additional file 4. Web-based analytics generated by the educational tool will be used to assess the utilization of the tool, which include data on content with which they engage, length of time spent on different content, and satisfaction ratings or feedback.

The measure of opinion and perspectives for participating the trial will be assessed via a phone- recorded interview (semi-structured) in both the eHealth and usual care group with the interviewee’s permission, for which a guide with open questions will be used to provide structure. The phone call will be made by a researcher who have experiences in qualitative interviews and is independent of the conduction of this trial. Two researchers (independent of the conduction of this trial) will be instructed by the interviewer to independently read and code transcribed texts line-by-line, from which codes generated will be sorted into themes and discussed to gain an overall understanding of any issue on difficulties and barriers to complete the trial. Any discrepancy will be resolved by the interviewer (senior researcher). During the trial, adverse events, medications and any other care received will be recorded using a log sheet, a sample could be found in Additional file 3.

##### Data integrity and monitoring

To assess trial safety and ensure that the best interests of participants will be observed at all times, an independent Data Safety Monitoring Committee will be assembled. Once 10, 50, and 80% of the sample size is reached, a data quality audit will be performed during the trial being conducted. Further, data will be stored in encrypted spreadsheets on secured servers hosted by the West China Hospital of Sichuan University, in which any potential risk of omissions and errors will be regularly scrutinized, and then exported to a statistical software for analysis by a statistician blinded to group allocation. All data collected in this trial will be restricted to the principal investigator and specific members of the research team using the backend of the database or servers.

##### Sample size

Sample size calculation was conducted based on the between-group difference on primary outcome, assuming that participants in the intervention group will have a correct response rate of 55.3% compared to that of 39.5% in the control group [27]. Based on a power of 95% and a 5% significance level (two-sided test), a value of 0.5 SD was used to ensure a large enough sample size. A Z-score of 1.96 was determined by applying these parameters. To allow for a dropout rate of 20%, a sample size of 108 per group (total of 216 participants) is required. Calculations were performed with PASS 15.0 (NCSS, LLC).

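### The sample-size paragraph does not reproduce 108 per group: at 0.5 SD and 20% dropout this gives 90% power, not the stated 95%, and 0.5 SD is not tied to the 15.8-point difference

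*Protocol article*

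**What the plan says.** Everything relevant is in one paragraph of the protocol article, under Sample size.

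- Assumed effect: "a correct response rate of 55.3% compared to that of 39.5% in the control group", a difference of 15.8 percentage points.
- Error rates and scale: "Based on a power of 95% and a 5% significance level (two-sided test), a value of 0.5 SD was used". The reason given for the 0.5 is that it makes the sample large enough.
- Quantile: "A Z-score of 1.96 was determined by applying these parameters".
- Result: "To allow for a dropout rate of 20%, a sample size of 108 per group (total of 216 participants) is required".

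The calculation is attributed to PASS 15.0. No other SD is given. The Primary outcome section defines the endpoint as a summed knowledge score, and the Statistical analysis section plans an independent t-test and ANCOVA for quantitative variables. Allocation is 1:1 (Randomization and allocation).

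**The concern.** Power, significance level, effect, dropout and sample size are all printed, so the result can be recomputed, and 108 per group looks too small for 95% power once a fifth of participants are lost.

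A second difficulty is that the paragraph names two effect descriptions, a 15.8-point difference in response rate and a value of 0.5 SD, without saying how they relate. A reader cannot tell whether 0.5 is the size of the effect in SD units or the SD itself.

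At stake is the stated justification for 216 participants on the primary outcome, and the weight a reader would give to a null result.

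**Working it through.** **Inputs (all from Sample size unless noted).** Two-sided alpha 0.05; power 0.95; 0.5 SD; rates 55.3% and 39.5%; dropout 20%; 108 per group. 1:1 allocation is from Randomization and allocation; the t-test is from Statistical analysis.

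**Step 1. Try to reproduce 108 with 0.5 as the standardised difference d.**

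Normal approximation: n = 2(z₀.₉₇₅ + z₀.₉₅)² / d² = 2(1.960 + 1.645)² / 0.25 = 103.96, so 104 per group. The exact calculation with the noncentral t gives 105.

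Inflating for dropout:

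| Evaluable per group | ÷ 0.8 | × 1.2 |
|---|---|---|
| 104 (normal) | 130 | 125 |
| 105 (t) | 132 | 126 |

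None of these is 108.

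**Step 2. Which departures from the stated inputs come close?**

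- 90% power, two-sided t-test, d = 0.5: 86 evaluable; 86 / 0.8 = 107.5, so 108. This is an exact match.
- 95% power, one-sided: 87 (normal) or 88 (t), inflated to 109 or 110. This is close, but it contradicts both the two-sided statement and the 1.96.

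**Step 3. Power that 108 randomised per group provides at d = 0.5.**

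After 20% dropout, 108 × 0.8 = 86.4, taken as 86. Noncentrality is d√(n/2) = 0.5 × √43 = 3.28.

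| Evaluable per group | Power (t-test) | Type II error |
|---|---|---|
| 86 | 90.3% | 9.7% |
| 105 | 95.0% | 5.0% |
| 108 (no dropout) | 95.5% | 4.5% |

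The ratio to the stated type II error is 9.7 / 5 = 1.94. Reaching 95% needs 105 of the 108 evaluable, a loss of 3 / 108 = 2.8%.

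**Step 4. Link 0.5 SD to the 15.8-point difference.**

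If 15.8 points equals 0.5 SD, the SD is 15.8 / 0.5 = 31.6 points. The document does not give this figure, so the SD has to be treated as an assumption. Power for 15.8 points with 86 evaluable per group (t-test):

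| Assumed SD (points) | d | Power |
|---|---|---|
| 25 | 0.632 | 98% |
| 28.7 | 0.551 | 95% |
| 31.6 | 0.500 | 90% |
| 50 | 0.316 | 54% |

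The last row takes 0.5 literally as the SD on the proportion scale (0.158 / 0.5 = 0.316). Comparing 55.3% with 39.5% as two proportions gives almost the same power, 54.6%.

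**Step 5. The Z-score sentence.** 1.96 is the two-sided 5% quantile and depends on alpha alone. The power quantile (1.645 for 95%, 1.282 for 90%) is not shown, so the sentence does not help to identify which power was used.

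**The case against.** The strongest reply is that the practical harm is small. On the reading most favourable to the plan, the trial still has 90% power. Statistical analysis also lists ANCOVA: if the baseline score were a covariate correlated about 0.43 with the outcome (√(1 − 86/105) = 0.43), 86 per group would give 95% at 0.5 SD. This stands as a limit on the consequences. It does not rescue the calculation, because Sample size assumes no such correlation.

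It can also be said that 1.96 is the correct quantile for alpha and that a condensed article need not print the other one. That is fair, and the sentence is only a minor wording point.

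Three stronger readings are tempting, and the documents do not support them.

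- *The trial has only about 54% power.* This requires an SD of 50 percentage points, essentially the largest possible for a score expressed as 0 to 100%, or a single yes/no endpoint per patient. The Primary outcome section defines a summed score, so 54% shows how far the wording can be stretched and is not a credible power estimate.
- *The trial misses 95% power for its own assumed difference.* That depends on the SD, which is not given. At an SD of about 28.7 points or less, 86 per group would reach 95% for 15.8 points.
- *108 was computed at 90% power and misreported, so 0.5 must be the standardised effect.* The exact match in Step 2 suggests this, but it is an inference. The stated purpose, "a value of 0.5 SD was used to ensure a large enough sample size", would also fit a deliberately conservative SD.

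Converting 31.6 points to questionnaire units is not supported either. The Primary outcome section gives 31 correct answers but a total of 0 to 21, so how a response rate maps to the total score is undefined.

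**Conclusion.** The point holds as an internal inconsistency: the stated power, standardised difference, dropout and sample size cannot all be true together, and nothing else in the protocol repairs this. At d = 0.5 the sample is short by 132 − 108 = 24 per group for 95% power, or equivalently the power is 90% where 95% is stated. The type II error is nearly double the claim, not at least double.

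These figures assume a two-sided 5% unadjusted t-test, equal groups, 20% dropout with no information recovered from those lost, and 0.5 as the standardised difference. Power for the 15.8-point difference itself cannot be fixed from the document because the SD is missing.

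This should be fixed. It does not show that the trial is badly underpowered.

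**What to change.** Keep 216 participants. Check the PASS inputs to establish whether 0.5 was entered as the standardised effect or as an SD, and which power was requested. Then restate the power to match.

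If 0.5 is the standardised effect, write: *86 evaluable per group (108 less 20% dropout) gives 90% power, two-sided 5%, for a standardised difference of 0.5.* Add the SD that links this to the 15.8-point difference (31.6 points if the two are meant to be equal).

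If 0.5 proves to be an SD on the response-rate scale, that sentence must not be used; report the power that follows from that SD instead.

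Either delete the Z-score sentence or give both quantiles. The public statistical analysis plan promised under Statistical analysis should carry the corrected figure.

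Cost: if 0.5 is the standardised effect, wording only, with a less favourable stated power and no extra participants. Holding to 95% at a standardised difference of 0.5 would instead need about 132 per group (264 in total).
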